**Table 6. Solicited local adverse reaction severity grading**

| Local Reaction to Injectable Product | Mild (Grade 1) | Moderate (Grade 2) | Severe (Grade 3) | Potentially Life Threatening |
|---------------------------------------------|-----------------------|---------------------------|-------------------------|-------------------------------------|
|---------------------------------------------|-----------------------|---------------------------|-------------------------|-------------------------------------|

|                                                           |                                          |                                                                                |                                                                           | (Grade 4)                             |
|-----------------------------------------------------------|------------------------------------------|--------------------------------------------------------------------------------|---------------------------------------------------------------------------|----------------------------------------------|
| Pain /Tenderness                                          | Does not interfere with routine activity | Interferes with routine activity or repeated use of non-narcotic pain reliever | Prevents routine daily activity or repeated use of narcotic pain reliever | Emergency room (ER) visit or hospitalization |
| Erythema/Redness
(Adolescents & adults, age ≥12yrs)    | Affected area 25 - < 50mm in diameter    | Affected area 50-<100mm in diameter                                            | Affected area ≥ 100 mm in diameter                                        | Necrosis or exfoliative dermatitis           |
| Erythema/Redness
(Children, age 2<12 yrs)              | < 25 mm in diameter                      | 25 – 50 mm in diameter                                                         | ≥ 50 mm in diameter                                                       | Necrosis or exfoliative dermatitis           |
| Erythema/Redness
(Children, age < 2 yrs)               | < 10 mm in diameter                      | 10 < 25 mm in diameter                                                         | 25 < 50 mm in diameter                                                    | ≥ 50 mm in diameter                          |
| Swelling/Induration
(Adolescents & adults, age ≥12yrs) | Affected area 25 - < 50mm in diameter    | Affected area 50-<100mm in diameter                                            | Affected area ≥ 100 mm in diameter                                        | Necrosis or exfoliative dermatitis           |
| Swelling/Induration
(Children, age 2<12 yrs)           | < 25 mm in diameter                      | 25 – 50 mm in diameter                                                         | ≥ 50 mm in diameter                                                       | Necrosis or exfoliative dermatitis           |
| Swelling/Induration
(Children, age < 2 yrs)            | < 10 mm in diameter                      | 10 < 25 mm in diameter                                                         | 25 < 50 mm in diameter                                                    | ≥ 50 mm in diameter                          |

|                                    |                                                                                                 |                                                                                                                                 |                                                                                       |    |
|------------------------------------|-------------------------------------------------------------------------------------------------|---------------------------------------------------------------------------------------------------------------------------------|---------------------------------------------------------------------------------------|----|
| Pruritis associated with injection | Itching localized to injection site that is Relieved spontaneously or with < 48 hours treatment | Itching beyond the injection site that is not generalized OR Itching localized to injection site requiring ≥ 48 hours treatment | Generalized itching causing inability to perform usual social & functional activities | NA |
|------------------------------------|-------------------------------------------------------------------------------------------------|---------------------------------------------------------------------------------------------------------------------------------|---------------------------------------------------------------------------------------|----|

All unsolicited adverse events observed by investigator and/or reported by participants/parent(s)/LAR after discussing with the investigator will be recorded in the eCRFs with their severity grading and relatedness to the study vaccine.

All SAEs irrespective of their causal association will also be graded for their severity.

---

#### 9.2.2 RELATIONSHIP TO INVESTIGATIONAL PRODUCT

For all collected AEs, the investigator who examines and evaluates the participant will determine the relationship of each AE with the investigational product based on plausible biologic mechanism, temporal relationship of occurrence after administration of the investigational product, identification of possible alternative etiologies including underlying disease, concurrent illness or concomitant medication, and his/her clinical judgment. The relationship of vaccination to adverse event (AE) will be determined based on the definitions below.

- **Definitely Related** – There is clear evidence to suggest a causal relationship, and other possible contributing factors can be ruled out. The clinical event, including an abnormal laboratory test result, occurs in a plausible time relationship to vaccine administration and cannot be explained by concurrent disease or other drugs or chemicals. The response to withdrawal of the Vaccine (dechallenge) should be clinically plausible.
- **Probably Related** – There is evidence to suggest a causal relationship, and the influence of other factors is unlikely. The clinical event, including an abnormal laboratory test result, occurs within a reasonable time after administration of vaccine, is unlikely to be attributed to concurrent disease or other drugs or chemicals, and follows a clinically reasonable response on withdrawal (dechallenge).

- **Possibly Related** – There is some evidence to suggest a causal relationship (e.g., the event occurred within a reasonable time after administration of vaccine). However, other factors may have contributed to the event (e.g., the participant clinical condition, other concomitant events). Although an AE may rate only as “possibly related” soon after discovery, it can be flagged as requiring more information and later be upgraded to “probably related” or “definitely related,” as appropriate.
- **Unlikely to be related** – A clinical event, including an abnormal laboratory test result, whose temporal relationship to vaccine administration makes a causal relationship improbable (e.g., the event did not occur within a reasonable time after administration of vaccine) and in which other drugs or chemicals or underlying disease provides plausible explanations (e.g., the participant clinical condition, other concomitant treatments).
- **Not Related** – The AE is completely independent of vaccine administration, and/or evidence exists that the event is definitely related to another etiology. There must be an alternative, definitive etiology documented by the clinician.

The criteria for determining causality can be documented as follows: The initial four definitions can be considered as ADR and the last one i.e. “Not Related” can be considered as Non-ADR.

---

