#### 9.1.1 DEFINITION OF ADVERSE EVENTS (AE)

**Adverse events (AE):** These are defined as any untoward medical occurrence which follows immunization and which does not necessarily have a causal relationship with the administration of the vaccine. An AE may be any unfavorable or unintended sign, symptom, abnormal laboratory finding or disease.

**Adverse Drug Reactions (ADR):** All noxious and unintended responses to a medicinal product related to any dose should be considered adverse reactions (AR). The phrase “responses to a medicinal product” means that a causal relationship between a medicinal product and an AE is exist with at least a reasonable possibility.

**Solicited AEs** are predetermined events, identified in the Investigator's Brochure (IB), which may reflect safety concerns related to the investigational product. AEs that will be solicited by the participant/ parents/LAR and recorded in the diary card and reviewed by a blinded observer during the 7 days after each dose for this study include:

- Local reactions at the site of injection: pain/tenderness, erythema/redness, induration/swelling, pruritus associated with injection
- Systemic reactions (adapted by age group): fever, lethargy, irritability, nausea/vomiting, arthralgia, diarrhea, drowsiness, loss of appetite, chills, headache, fatigue, myalgia and persistent crying

Among the various systemic reactions headache, fatigue, myalgia will be captured only for 2 to 45 years subjects while persistent crying will be captured only for 6 months to 2 years subjects. The rest of the systemic reactions will be captured in all age strata. This is also clearly mentioned in the diary cards.

**Unsolicited AEs** are all other adverse events (those that do not fall under the categories of solicited Adverse Reactions) that are identified by site staff, the site investigator and the Safety Medical Monitors. These unsolicited AEs will be documented in the participant's study records and entered in the study eCRFs.

Results will be expressed as frequency of the AEs and individual descriptions will be tabulated according to MedDRA organ class system.

---

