### 11.5.3 SAFETY ANALYSIS

The following safety endpoints will be descriptively summarized by each formulation and overall and within each age stratum.

- Local and systemic solicited adverse events during the 7 days after each dose:

- the solicited local reactions at the site of injection: pain, tenderness, erythema/redness, swelling/ induration, pruritus and
- solicited Systemic reactions (adapted to each age group): fever, lethargy, irritability, nausea/vomiting, arthralgia, diarrhea, drowsiness, loss of appetite, chills, headache, fatigue, myalgia and persistent crying
- Unsolicited adverse events during 4 weeks (28 days) after vaccination
- Serious Adverse Events during the entire study period

Number of AEs and proportion of participants with safety endpoints after Vi-DT (MD), Vi-DT (SD), and Control vaccine will be summarized and the 95% confidence interval of the proportion will be calculated for Vi-DT (MD), Vi-DT (SD), and Control vaccine within each age stratum as well as overall strata.

Occurrence of any SAE during the study and AE that lead participant early drop out of the study will be listed.

---

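### Two classification rules in protocol section 9 contradict the protocol's own text: *Unlikely* events count as adverse reactions, and 50 mm at ages 2 to under 12 has two grades

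*Protocol*

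**What the plan says.** **Causality.** Section 9.1.1 describes an adverse drug reaction as a response for which "a causal relationship between a medicinal product and an AE is exist with at least a reasonable possibility". Section 9.2.2 has five categories: definitely, probably and possibly related, unlikely to be related, and not related. The *Unlikely* category is for an event "whose temporal relationship to vaccine administration makes a causal relationship improbable", and for which other drugs or underlying disease offer plausible explanations. The section closes with the grouping "The initial four definitions can be considered as ADR and the last one", *Not Related*, as the only non-ADR category.

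**Local-reaction grades.** In Table 6, for ages 2 to under 12, redness is Grade 2 at "25 – 50 mm in diameter" and Grade 3 at "≥ 50 mm in diameter". The swelling row for that age band has the same bounds. The row for age 12 and over uses an open upper bound instead, with Grade 2 given as "Affected area 50-<100mm in diameter".

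**Use of these rules.** Section 9.1.3 defines a SUSAR as a kind of serious adverse reaction. Section 9.2.1 states that all solicited events will be graded, and section 5.1 refers the solicited-event endpoint to Tables 5 and 6. The planned summary in section 11.5.3 reads: "Number of AEs and proportion of participants with safety endpoints after Vi-DT (MD), Vi-DT (SD), and Control vaccine will be summarized".

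**The concern.** An event cannot be causally improbable and also carry a reasonable possibility of causation, so sections 9.1.1 and 9.2.2 give different answers for the same *Unlikely* event. This matters in two places. First, ADR status is part of the SUSAR definition, and SUSAR status sets the reporting clocks in section 9.4.2. Second, any table of related events will depend on which section the programmer follows.

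The 50 mm overlap is a smaller problem of the same kind. Two assessors who both follow Table 6 can give the same child a moderate or a severe reaction. Describing safety is a secondary objective (section 4), and section 3.3 says the trial is meant to contribute to a prequalification safety database, so severity tables should not rest on an undefined cut.

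**Working it through.** There is no stated figure to reproduce. The check compares the rules and then sizes the overlap.

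**Step 1: one event under each causality rule.** Take a serious, unexpected event that is neither fatal nor life-threatening and that the investigator judges *Unlikely*.

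| | Under 9.1.1 | Under the 9.2.2 grouping |
|---|---|---|
| Adverse reaction? | No: improbable is short of a reasonable possibility | Yes: fourth of the first four categories |
| Potential SUSAR (9.1.3)? | No | Yes |
| Report to the national regulator (9.4.2) | With the annual report | Within 15 calendar days |
| Report to the sponsor's IRB (9.4.2) | With the annual renewal report | Within 24 hours, excluding weekends and holidays |

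The two sections therefore lead to different reporting of the same event.

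**Step 2: whole-millimetre check of Table 6.** Each diameter from 1 to 150 mm was assigned to every grade whose bounds include it. Redness and swelling share the same bounds within each age row.

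| Age row | Diameters with two grades | Diameters with no grade |
|---|---|---|
| Under 2 | none | none |
| 2 to under 12 | 50 mm (Grades 2 and 3) | none |
| 12 and over | none | 1 to 24 mm |

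Only the 2 to under 12 rows overlap, and only at one value. The last column shows a gap: at age 12 and over Grade 1 starts at 25 mm, so a smaller reaction cannot be graded although section 9.2.1 says every solicited event will be.

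**Step 3: size of the overlap.** Planned numbers in the 2 to under 18 stratum are 250 per Vi-DT group and 100 in control (Group Allocation table and Table 1). The change in a Grade 3 proportion is k/n, where k is the number of children whose grade turns on a reading of exactly 50 mm.

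- k = 1: 1/250 = 0.4 points in a Vi-DT arm; 1/100 = 1.0 point in control.
- k = 5: 5/250 = 2.0 points in a Vi-DT arm; 5/100 = 5.0 points in control.

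The protocol gives neither the frequency of a 50 mm reading nor the number of children aged 2 to under 12. The age-strata reassignment lets this stratum shrink in favour of adults, and the step per child grows as n falls.

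**Step 4: what depends on these rules.** Sections 11.2 and 11.5.3 plan counts and proportions of solicited, unsolicited and serious events. Causality does not enter them, and a change between Grade 2 and Grade 3 leaves a reaction counted. The anti-Vi IgG endpoints use neither rule.

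**The case against.** The strongest reply is that no planned result changes. The protocol names no ADR rate and no Grade 3 rate as an endpoint or summary, and adverse events are documented whatever their relationship (section 9.3). The five-level causality judgement is kept for each event. The grouping sentence is permissive, and if it errs, it errs toward reporting more. The overlap is a single value in one age band, falls on all arms alike, and diary cards are reviewed by a blinded observer. All of this stands, and it limits the point to ambiguity in classification and reporting.

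A reader might infer that reaction and severe-reaction rates are distorted, or that ADR rates are inflated by a large, calculable amount. The documents do not support either reading. Appendix ii gives unsolicited-event rates in Phase II infants and toddlers (61.40% and 68.42%), but nothing says what share of affected participants would have only *Unlikely* events, so any inflation figure would rest on an unsourced assumption about a rate that the protocol does not plan to report. Nor are *Unlikely* events unrelated in substance: *Not Related* is a separate category that requires a documented alternative cause.

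A reader might also infer that the 2 to under 18 tables must be split at age 12 because the grading bounds differ. Table 6 openly sets severity scales by age, and randomisation within strata should balance the age mix across arms on average. Splitting the tables is a layout preference. Only the missing grade below 25 mm remains.

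The objection does not remove the contradictions themselves. SUSAR classification and the grading of solicited local reactions are working rules, and each currently gives two answers for the same case.

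**Conclusion.** The point holds as two internal contradictions plus one grading gap.

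- **ADR rule.** Sections 9.1.1 and 9.2.2 disagree on *Unlikely* events. The effect falls on SUSAR classification and on any ADR table that is produced. Its size cannot be stated from the documents.
- **50 mm boundary.** At ages 2 to under 12, one diameter has two grades for both redness and swelling. Each affected child is worth 0.4 points in a Vi-DT arm or 1.0 point in control on the stratum's Grade 3 proportion, assuming planned sizes and that such a proportion is tabulated. There is no set direction.
- **Below 25 mm at age 12 and over.** These reactions have no grade, contrary to section 9.2.1. Incidence would be affected only if ungraded reactions were left out of the counts, and the protocol does not say whether they would be.

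The two contradictions leave the planned AE and SAE incidences regardless of causality unchanged, and the equivalence conclusion is not affected at all. The matter should be corrected, but it concerns documentation and safety tabulation and is of low to moderate weight.

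**What to change.** 1. Reconcile sections 9.1.1 and 9.2.2 so that one ADR rule governs both tabulation and SUSAR classification under 9.1.3 and 9.4.2. Which rule to adopt is a safety-reporting decision for the sponsor. Either way, show *Unlikely* as its own row in any relatedness table so that readers can regroup.
2. Before database lock, make the Table 6 bounds for ages 2 to under 12 non-overlapping, for redness and swelling, so that 50 mm has one grade.
3. Reconcile the statement in 9.2.1 that all solicited events are graded with the missing grade under 25 mm at age 12 and over. One way is to tabulate those reactions as below Grade 1, so that they still count in incidence.

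The cost is minor wording changes and a re-derivation from recorded causality and diameters. Causality is already recorded for each event (section 9.3), and a ruler is issued with the diary card (Visit 2). Re-deriving grades assumes that the measured diameter, and not only its grade, was captured.

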### 9.2.3 EXPECTEDNESS

The Study Medical Monitor in consultation with site PI will be responsible for determining whether an AE is expected or unexpected. An Adverse Reaction will be considered unexpected if the nature, severity, or frequency of the event is not consistent with the risk information previously described for the study agent.

## 9.3 TIME PERIOD AND FREQUENCY FOR EVENT ASSESSMENT AND FOLLOW-UP

All participants will be observed for immediate local and systemic reactions for 30 minutes after each vaccination. For 7 consecutive days (Days 0-6) after each dose of study vaccine, the participant/parent(s)/LAR will be asked to record solicited local and systemic symptoms in the diary card. The study staff will remind participant/parent(s)/LAR of the importance of properly filling the diary cards and to return the cards at the next scheduled study visit. If they did not fill up or lost their card, the parent(s) or legal guardian will be interviewed for recall of symptoms with trained study staff during clinic visit on Day 7 after vaccination.

The occurrence of an adverse event (AE) will come to the attention of study personnel during study visits and interviews of a study participant presenting for medical care, or upon review by a study monitor.

All AEs including local and systemic reactions not meeting the criteria for SAEs will be captured on the appropriate case report form (eCRF). Information to be collected includes event description, time of onset, symptoms and physical examination findings, clinician's assessment of severity, relationship to study product (as assessed by the SI), medications given and time of resolution/stabilization of the event. All AEs occurring while on study will be documented appropriately regardless of relationship.

Changes in the severity of an AE will be documented to allow an assessment of the duration of the event at each level of severity to be performed. AEs characterized as intermittent require documentation of onset and duration of each episode.

The investigator will record all reportable events with start dates occurring any time after informed consent is obtained until the last day of study participation. At each study visit, the investigator will inquire about the occurrence of AE/SAEs since the last visit. Events will be followed for outcome information until resolution or stabilization.

## 9.4 REPORTING PROCEDURES

### 9.4.1 ADVERSE EVENT RECORDING AND REPORTING

Adverse events, solicited AEs, and SAEs will be assessed at various study visits, documented in the source record, and recorded in the eCRF using accepted medical terms and/or the diagnosis that accurately characterize the event. When the diagnosis is known the AE term recorded in the eCRF will be the diagnosis rather than constellation of symptoms. The SI will assess all AEs for seriousness, relationship to investigational product, severity, and other possible causes.

The timeframe for the collection of adverse events (AEs) occurring from the first administration of investigational product through Visit 4 for all study groups and will be collected as well as recorded in the source document and eCRF. However SAEs will be collected and recorded throughout the study period i.e. starting from the first administration of investigational product through to the end of the trial.

When an AE has not resolved by the current visit it will be documented in the eCRF as ongoing. Documentation will include date of onset, detailed description of the event and relevant history and physical examination, severity, attribution of the AE, treatment given and date the AE improved or resolved. The medical monitor will review the AEs reported regularly and clarify with SI if there are queries. The data manager will review all AEs for consistency and provide summary of AEs to the medical monitor periodically. Non-clinically significant AEs still ongoing as the end of the study will be listed as continuing. SAEs continuing at the end of the study will be followed to resolution or stabilization. Details of AE reporting are included in the MOP.

The PI, SI, and site staff will exercise due diligence in ascertaining, accurately recording and promptly entering data on the eCRF for all AEs of all study participants. As data becomes available from the participant, the clinic and laboratories, adverse events should be recorded and entered by the site staff on regular basis. Site investigators will review, in a timely manner, the AE source data and determine the severity of the event and relation to the study agent. Site investigators will contact the study medical monitor for consultation of AEs as required.

---

